## Abstract

**Background:**

Diabetic foot ulcers (DFUs) cause significant morbidity affecting 19% to 34% of people living with diabetes mellitus. DFUs not only impair quality of life but may also result in limb loss and mortality. Patient education has been advocated to raise awareness of proper foot self-care and the necessity of seeking assistance when a foot wound occurs. Modern technologies, including mobile health (mHealth) interventions such as health apps, bring the potential for more cost-effective and scalable interventions.

**Objective:**

This study aims to examine the feasibility and usability of a newly developed mHealth app called Well Feet, which is a diabetes and foot care education app for individuals at risk of developing DFU.

**Methods:**

Well Feet was developed using an evidence-based and expert panel cocreation approach to deliver educational content available in 3 languages (ie, English, Chinese, and Malay) via animation videos and a range of additional features, including adaptive learning. A nonrandomized, single-arm feasibility study using a mixed methods approach with a series of validated questionnaires and focus group discussions will be conducted. In total, 40 patients and carers will be recruited from a tertiary hospital diabetes clinic to receive a 1-month mHealth intervention. The primary outcomes are the usability of the app and a qualitative perspective on user experience. Secondary outcomes include changes in foot care knowledge, self-management behaviors, and quality of life.

**Results:**

Patient recruitment began in July 2023, and the intervention and data collection will be completed by the end of September 2023. This study has been approved by National Healthcare Group Domain Specific Review Board (2022/00614) on February 10, 2023. The expected results will be published in spring 2024.

**Conclusions:**

Through this feasibility study, the Well Feet DFU education app will undergo a comprehensive quantitative and qualitative evaluation of its usability and acceptance for future improvement in its design. With local contextualization, cultural adaptation, and its multilingual functionality, the app addresses a critical aspect of DFU health education and self-management in a multiethnic population. Findings from this study will refine and enhance the features of the app based on user feedback and shape the procedural framework for a subsequent randomized controlled trial to assess the effectiveness of Well Feet.

**Trial Registration:**

ClinicalTrials.gov NCT05564728; https://clinicaltrials.gov/study/NCT05564728

**International Registered Report Identifier (IRRID):**

DERR1-10.2196/52036

## Introduction

### Background

According to the International Diabetes Federation, 537 million people worldwide (ie, 1 in 10) lived with diabetes in 2021, and this number is expected to rise to 783 million by 2045 [1]. The lifetime incidence of developing a diabetic foot ulcer (DFU) in adults living with diabetes ranges from 19% to 34% [2]. In a 2017 systematic review and meta-analysis, DFU's global prevalence among people with diabetes was estimated to be 6.3%, with Asia having a prevalence of 5.5% [3]. Diabetes-related lower extremity complications affected an estimated 131 million people (1.8% of the total global population) in 2016, with overall age-standardized rates for years lived with disability increasing by 15.9% between 1990 and 2016 [4]. Southern sub-Saharan Africa, South Asia, and Southeast Asia experienced the greatest growth during the period. Despite multiple clinical [5], economic [6,7] and policy [8,9] attempts to address DFU in Singapore, the country is still struggling to combat the rising prevalence of DFU-related complications with a reported 1500 DFU-related lower-limb amputations performed each year [10]. Furthermore, the estimated recurrence rate is 22.1% per person-year [11]. Hence, DFUs impose a significant clinical and economic burden on health care systems around the world as well as significant reductions in the quality of life for those affected [12].

Prevention initiatives, including lifelong patient education and continuous empowerment, are key strategies for successful foot care and management of diabetes, as recommended by evidence-based guidelines [13]. Whether delivered one-to-one or in small groups, diabetes foot health education is resource-intensive and costly—requiring the participation of doctors, nurses, podiatrists, diabetes educators, and allied health professionals. While valuable, foot care and diabetes education sessions lack immediacy, timeliness, access, and flexibility. In Singapore, 36% of patients with diabetes reported receiving no diabetes education [14] and over 51% spend less than a minute checking their feet [15]. Given the unmet need, financial and health workforce constraints, and being in line with modern approaches to education and self-management support, a digitally supported diabetes education mobile health (mHealth) apps using prevention and management of the DFU education program carries the potential to improve health care delivery and increase uptake, equity, and cost-effectiveness of health services related to DFU. Patient-facing technology such as mHealth apps can be blended with face-to-face care to augment the overall delivery of care and health services [16] and impact patients’ health outcomes [17].

The other agency that is heavily involved in the management of DFU is the carer. Informal carers are defined broadly as any family member, partner, or friend who provides support to a person having a chronic condition. Carers play a vital role particularly in assisting with wound care, monitoring changes, ensuring foot hygiene, managing medications, offering emotional support, advocating for medical care, and providing education [18]. Carer’s involvement improves patient outcomes, prevents complications, and enhances overall DFU care and well-being. For many people with chronic conditions, particularly the elderly, informal carers provide support and take responsibility for many of the care needs. Upskilling informal carers may result in better health outcomes [18]. Training equips them with skills to provide effective wound care, identify issues early, prevent complications, manage medications, offer emotional support [19] and promote timely access to health care. This improves the overall DFU management beyond the hospital walls, which may eventually result in reduction of hospitalizations, lowers costs of health care, and ensures collaborative, sustainable DFU management among patients, carers, and health care professionals.

### Related Work

Studies suggest that people living with diabetes show an interest in mHealth apps for preventing and monitoring DFUs [20]. There is a growing body of evidence supporting the potential of mHealth apps to enhance diabetes self-management performance [21]. A few studies have been conducted to assess or validate the potential of an mHealth app for diabetic foot care. Some of them focus on providing wound care trackers [22,23], others on empowering with knowledge on foot-ankle exercises [24], quick tips on foot care and first aid, reminders for medical check-ups, a contacts feature to save health providers’ contact information [25], text messaging [26], foot care essentials [27,28], foot care education in 6 animations [29] and tips for self-assessment [30]. Prior to a full trial, feasibility studies are routinely performed to determine whether a future study is feasible [31].

Some of the challenges identified in such interventions include maintaining patient engagement [25], tailoring content to the different stages of complexity of the disease, retaining and applying the knowledge acquired [32]. Thus, there is a need to explore the mechanisms by which evidence-based behavior change techniques and digital features can influence the uptake of digital diabetes and foot care education and ultimately improve diabetes health literacy and self-management behaviors. Even though the validation studies presented promising results, none of the mHealth apps for DFU comprise comprehensive in-depth education on all aspects of foot health, including prevention, inspection, and wound care while concurrently providing support for self-management with tracking features that focus both on feet health and general diabetes care. Additionally, no other tool addresses the need for a multilingual and adaptive solution that fits individual needs, such as the role (patient or caregiver), severity of the condition, and competency levels, concurrently reinforcing learning through notifications and spaced learning. Finally, there is a necessity to understand the user’s engagement and app effectiveness in detail using granular click-level data.

### Aim

This is a “proof-of-concept” feasibility study to evaluate a foot health education app for people living with diabetes, Well Feet, among patients and carers. Prior to a full trial, feasibility studies are routinely performed to determine whether a future study is feasible [31].

## Methods

### Study Design

This study is a nonrandomized, single-arm feasibility study with baseline, end point, and focus-group discussion design. An explanatory sequential mixed methods approach will be used to assess feasibility and usability of the mHealth app, Well Feet. Our study features a 1-month intervention period carefully designed to strike a balance between meaningful observation and participant convenience. This timeframe enables us to assess the feasibility of the intervention on our selected outcomes. All participants will receive Well Feet, and their feedback will be collected through quantitative and qualitative rating measures. Subsequently, focus group discussions will be conducted to provide valuable insights into their experiences. The reporting of this protocol follows CONSORT (Consolidated Standards of Reporting Trials) 2010 statement extension for feasibility studies [33]. This study has been registered at ClinicalTrials.gov (NCT05564728).

### Study Participants

#### Eligibility Criteria

Both patients and carers will be invited to participate in this study. Inclusion criteria for patients are (1) being diagnosed with type 2 diabetes and attending Tan Tock Seng Hospital Diabetes Clinic, (2) being 21 years or older, (3) being able to speak and read English, (4) owning a smartphone or tablet and can download the app, (5) having internet access, (6) being able to provide informed consent, (7) being Singaporeans or Singapore permanent residents. Inclusion criteria for carers are (1) carers who provided care for a patient with type 2 diabetes for the past 6 months, (2) being aged 21 years or older, (3) being able to speak and read in English, (4) owning a smartphone or tablet and being able to download the app, (5) having internet access, and (6) being able to provide informed consent. Exclusion criteria for patients and carers include being (1) pregnant, (2) an inpatient, or (3) having received formal training in medicine or allied health services.

#### Recruitment

Patients will be recruited through referrals from attending endocrinologists at Tan Tock Seng Hospital. Recruitment will take place during the patients’ routine clinic visits at Diabetes Clinic. The endocrinologists will screen for potential participants’ eligibility based on this study’s inclusion and exclusion criteria before referring them to the appointed research assistant to complete the recruitment process. At the same time, patients will be asked to nominate their carers to participate in this study. The nomination is optional and subject to patients’ and carers’ willingness. Notwithstanding, patients without a carer can still participate in this study. Potential patients and carers who choose not to participate in this study will be asked an open-ended question about the reasons. It will be highlighted that answering the question is voluntary. The information will be used to inform about the barriers to recruitment and acceptability of the intervention.

#### Informed Consent

The research assistant will conduct a briefing for all referred patients and carers in a closed space outside of the clinic room. The briefing involves explaining this study’s aim and study’s inclusion and exclusion criteria. Additionally, potential participants will be briefed thoroughly about this study’s procedures, risk exposure, and all the information included in the informed consent form (Multimedia Appendix 1). The research assistant will provide adequate time for the participants to decide. Participants will be allowed to discuss their decisions with family members before participating in this study. The wishes of the participant will be respected if they choose not to participate in the research. The research assistant or site principal investigator will provide a copy of the informed consent form and obtain written consent from the potential study participants. It will be highlighted to the participants that this study is voluntary, and their participation would not affect their clinical care or any benefits that they are entitled to.

Participants will be advised to retain a copy of the signed informed consent form for documentation, they will also receive a WhatsApp (Meta Platforms, Inc) message confirming their enrollment for this study, contact details, and basic information about study design.

### Sample Size and Power Calculation

Since this is a feasibility study, a formal sample size calculation is not required [34]. Our target is to recruit a minimum of 30 participants (with a maximum of 40), evenly divided into groups: persons living with diabetes and carers of persons living diabetes, with 15 participants in each group (with a maximum of 20). This approach is based on a previous study that shows a feasibility study requires 30 or more participants to estimate a parameter [35]. An arbitrary sample size of 30 would provide 0.75 (75%) power to detect a medium effect size of 0.5. Alternatively, a sample size of 40 would provide even greater power at 0.87 (87%).

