### Analysis

#### Quantitative Analyses

The questionnaires answered by the participants will be summarized using descriptive statistics, and the data will be presented as frequencies, percentages for categorical variables and means, SDs, medians, and IQRs for continuous variables depending on the distribution of the variable. Descriptive statistics will also be used to assess measures of app usage. Differences between groups will be analyzed using chi-squared or Fisher exact test for nominal data and changes within the groups over time (pre-post) will be analyzed using the Wilcoxon signed rank test. R (R Core Team) and Stata (StataCorp) will be used for all analyses.

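### The stated power of 75% (n=30) and 87% (n=40) fits a test on all participants pooled, not the planned tests within patients and within carers, where it is about 42% and 54%

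*Protocol article*

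**What the plan says.** All references are to the protocol article.

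- **Sample Size and Power Calculation:** no formal calculation is considered necessary for a feasibility study. On size: "Our target is to recruit a minimum of 30 participants (with a maximum of 40), evenly divided into groups", namely people living with diabetes and carers, "with 15 participants in each group (with a maximum of 20". Then: "An arbitrary sample size of 30 would provide 0.75 (75%) power to detect a medium effect size of 0.5". For 40 participants the stated power is 0.87. No test, significance level, sidedness, endpoint or dropout allowance is given.
- **Quantitative Analyses:** "changes within the groups over time (pre-post) will be analyzed using the Wilcoxon signed rank test". For comparisons between groups: "Differences between groups will be analyzed using chi-squared or Fisher exact test for nominal data".
- **Study Design:** "This study is a nonrandomized, single-arm feasibility study with baseline, end point, and focus-group discussion design".
- **Outcome Measures and Table 1:** the primary outcomes are the mHealth App Usability Questionnaire (MAUQ), at the end of the trial, and qualitative experience from focus groups. Changes in foot care knowledge, self-management behaviors and quality of life are secondary.

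**The concern.** A power figure describes a particular test on a particular number of people. Here the power figures are attached to the total sample, while the only pre-post test in the document is planned within groups, and the only groups defined are patients and carers. Each such test uses half of the sample that the power statement refers to.

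The figures cannot belong to the primary outcomes either. The MAUQ is measured once, so it has no pre-post change, and the other primary outcome is qualitative. That leaves the secondary pre-post changes as the natural home of the power claim.

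What is at stake is interpretation. The Principal Findings section expects a pretest-posttest difference in knowledge. A reader who accepts 75% to 87% power could give a null result in patients or in carers more weight than it deserves.

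**Working it through.** **Inputs from the document:** effect size 0.5; total 30 or 40; group size 15 or 20; Wilcoxon signed rank test within groups.

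**Assumed, because not stated:** two-sided 5% level, normally distributed differences, complete end point data, effect size read as mean change divided by the SD of the change.

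**Step 1. Reproduce the stated figures.** For a paired (equivalently one-sample) t-test, power is P(|T| > t(0.975, n−1)), where T is noncentral t with n−1 degrees of freedom and noncentrality 0.5 × √n.

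- n=30: noncentrality 0.5 × √30 = 2.74; power 0.754. Stated: 0.75.
- n=40: noncentrality 0.5 × √40 = 3.16; power 0.869. Stated: 0.87.

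Other readings do not round to both stated figures:

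| Reading | n=30 | n=40 |
|---|---|---|
| One-sided 5% paired t | 0.848 | 0.928 |
| Normal approximation, two-sided | 0.782 | 0.885 |
| Chi-squared, w=0.5, 1 df | 0.782 | 0.885 |
| Wilcoxon signed rank, all pooled (simulated) | 0.736 | 0.857 |

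**Step 2. Apply the planned test at the planned group size.** Wilcoxon power was obtained in two ways: as t-test power at an effective sample size of n × 3/π, and by simulating the exact test (100,000 runs).

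| Per group | Paired t | Wilcoxon, 3/π adjustment | Wilcoxon, simulated |
|---|---|---|---|
| 15 | 0.438 | 0.419 | 0.420 |
| 20 | 0.565 | 0.543 | 0.545 |

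**Step 3. Split the shortfall.**

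- Total 30: 75.4% to 43.8% from using 15 instead of 30 (31.6 points), then to 42.0% from Wilcoxon instead of t (1.8 points).
- Total 40: 86.9% to 56.5% from using 20 instead of 40 (about 30 points), then to 54.5% from Wilcoxon instead of t (2.0 points).

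**Step 4. Sensitivity to sidedness.** With a one-sided 5% level, within-group Wilcoxon power is about 0.56 (n=15) and 0.68 (n=20), still well below 0.75 and 0.87.

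**Step 5. Precision.** The half-width of a 95% confidence interval for a mean change, in SD units of the change, is t(0.975, n−1)/√n.

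- n=15: 2.145/3.873 = 0.55
- n=20: 2.093/4.472 = 0.47

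**The case against.** **The power claim carries little weight in this study.** The protocol calls the size arbitrary, bases it on a rule for feasibility studies, and treats the pre-post changes as secondary. No progression rule depends on 75% or 87%. The limitations section already says that the cohort is small and that a multicenter randomized trial is warranted. The Results section reports 40 enrolled, so the 15-per-group case is the unused minimum. All of this stands, and it sets the severity.

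**A pooled analysis may have been intended.** The study is single-arm and the outcomes are described jointly for patients and carers. If so, the stated figures are roughly right: a pooled Wilcoxon test has about 74% and 85% to 86% power. This also stands, but the analysis section does not describe a pooled test. It refers to changes within the groups, directly after differences between groups.

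**Stronger readings that the document does not support:**

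- A reader might infer that the study is too small. The sample size was not derived from this power, so an incorrect power figure does not show that.
- A reader might see the 30-participant rule as broken by groups of 15. The protocol states that rule for the study as a whole, and a total of 30 meets it.
- A reader might cite low power for comparing mean scores between patients and carers. No such comparison is planned; the between-group tests are for nominal data.
- A reader might blame the choice of the Wilcoxon test. It accounts for only about 2 of the 33 points.
- A reader might take the pooled paired t-test as the authors' stated method. It is inferred from the match of both figures.

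**Conclusion.** The power statement does not describe the analysis that the article plans. For a standardized change of 0.5, the within-group signed rank test has about 42% power with 15 per group and 54% with 20, against the stated 75% and 87%. A true change of that size would be missed in about 58% or 46% of cases.

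This rests on reading the groups as patients and carers, and on the assumptions listed with the calculation. For the 54% it also needs an even split of the 40 enrolled, which the Results section does not report. Questionnaire completion is voluntary, so missing end point data would lower these figures further.

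The severity is minor to moderate: the figures mislead about the secondary pre-post results but affect neither the primary outcomes nor the basis of the sample size.

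**What to change.** Any one of these is enough:

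1. **Restate power per group.** For example: within each group of 15 (20), the signed rank test has about 42% (54%) power to detect a standardized change of 0.5, assuming a two-sided 5% level, normally distributed differences and no attrition.
2. **Replace power with precision.** Give the expected 95% confidence interval half-width for a mean change: 0.55 SD with 15 per group and 0.47 SD with 20. This suits a feasibility study best.
3. **Specify a pooled pre-post test,** if that is what was meant. State it in Quantitative Analyses and attach the figures to it: about 74% and 85% for a pooled Wilcoxon test. These treat all participants as independent. Because patients may nominate their own carers (Recruitment section), the text should say how patient-carer pairs are handled.

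The cost is wording only, with no extra participants or data. Under the first two options the stated position becomes less favorable.

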### Intervention

#### Well Feet mHealth App

Well Feet is a diabetes and foot care education mHealth developed by Nanyang Technological University. The technical building process of the app is outsourced to a university-appointed vendor while the content building process was carried out in-house. The app was made available to download both for iOS and Android. Screenshots of Well Feet’s main interface and features are shown in Figure 1.

**Figure 1 figure1:**
[figure not shown]
Selected screenshots from the Well Feet app.

#### Adaptive Learning Framework

Well Feet is a diabetes and foot care education app and was designed based on an adaptive learning framework to deliver educational modules and action-oriented conversations related to foot care through multilingual (English, Mandarin, and Malay) animations with a deep fake presenter. A total of 21 modules covering 4 themes: introduction, inspection, prevention, and wound care, have been developed by this study’s team based on a series of validated and evidenced-based sources including the International Working Group on the Diabetic Foot [36] guidelines as visualized in Textbox 1. The curriculum outline was consulted in 2 rounds in an asynchronous expert panel. Next, the scripts were developed with consideration of readability, cultural relevance, and local context, and were transformed into animations in an iterative design process comprising storyboarding, prototyping, production, and reviews. In total, 54 bite-sized and visually appealing animation videos ranging from 30 seconds to 2 minutes were produced for diabetes foot educational content. The content was prepared in English and translated into Mandarin and Malay. The animations are accompanied by adaptive learning quiz questions that allow us to assess knowledge gaps and trigger spaced learning conversations in case of incorrect answers. The system includes storing an in-depth click-level data which allows a vast analysis of learning and usage analytics.

Overview of the 21 modules included in the Well Feet app.
